### **4.6 Declaration of interests**

[name] (IH), [name] (SG), [name] (Rds) and [name] are employed by the AOANJRR. [name] (NP)'s salary is partly supported by the MRFF grant received for CRISTAL.

### **4.7 Data access**

All principal investigators involved in data analysis will have access to deidentified datasets. All principal investigators involved in subcommittees will have access to relevant deidentified data necessary for undertaking their specific role (e.g. outcome validation).

### **4.8 Additional care**

As both interventions are standard, recommended practice, no additional treatment will be provided for participants.

#### **4.9 Dissemination**

A writing committee will be established to write the principal papers (primary and secondary outcomes). Dissemination will be by peer reviewed journal publication, conference presentation and through media. All study findings will be reported, regardless of statistical significance or the size or direction of effect.

Study findings will be released to participating sites and investigators.

Input will be sought into guideline development by state and national bodies (e.g. ACSQHC). The results of the study are expected to be published in a journal with high impact and to be of interest to a wide audience (beyond orthopaedics and haematology, including hospitalists and public health). They are expected to have clinical importance and statistical power that will enable the results to influence practice, which currently lacks studies on this size and quality.

#### **4.10 Implementation**

Surgeons will be surveyed prior to commencement (separate study) to assess their willingness to change practice based on the results of the trial, allowing for current practice, study findings, experience, gender.

Following the study, practice change at departmental and surgeon level will be measured for each surgeon at each site by assessing departmental and individual surgeon prophylaxis methods.

Practice change more broadly will be assessed through data linkage, assessing the increase or decrease in post-operative LMWH prescriptions.

#### **4.11 Authorship**

Authorship for principal papers will be by the members of the writing committee and the CRISTAL Study Group (consisting of all investigators according to the authorship guidelines of the ICMJE).

#### **5. Statement for compliance with NHMRC National Statement on Ethical Conduct of Research Involving Humans**

This study will be conducted in accordance with the ethical principles that have their origin from the Declaration of Helsinki and are consistent with ICH/GCP. This study will comply with National Health and Medical Research Council (NHMRC) National Statement on Ethical Conduct in Research Involving Humans.

### **1. Administrative information**

#### **1.1. Registration**

CRISTAL has been registered with the Australian and New Zealand Clinical Trials Registry (anzctr.org.au, ACTRN12618001879257).

#### **1.2. Funding**

This study is fully and solely funded by a 4-year Medical Research Futures Fund Lifting Clinical Trials and Registries Capacity Grant (Application ID: APP1152285) awarded in January 2018. The funding source had no role in the design of this study and will not have any role during its execution, analyses, interpretation of the data, dissemination or decision to publish.

The day to day management of the trial will be the responsibility of the Australian Orthopaedic Association National Joint Replacement Registry (AOANJRR) and South Australian Health & Medical Research Institute (SAHMRI).

Other expert subgroups may be established throughout the project to advise on specific elements and make recommendations should the need arise.

## **1.6. Abbreviations**

|         |                                                                        |
|---------|------------------------------------------------------------------------|
| AOANJRR | Australian Orthopaedic Association National Joint Replacement Registry |
| AAOS    | American Academy of Orthopaedic Surgeons                               |
| ACORN   | Arthroplasty Clinical Outcomes Registry                                |
| DVT     | Deep Venous Thrombosis                                                 |
| ICJME   | International Committee of Medical Journal Editors                     |
| LMWH    | Low Molecular Weight Heparin                                           |
| NICE    | National Institute of Health and Care Excellence                       |
| NOAC    | Novel Oral Anticoagulant                                               |
| OA      | Osteoarthritis                                                         |
| PE      | Pulmonary Embolus                                                      |
| PROMs   | Patient Reported Outcome Measures                                      |
| THA     | Total Hip Arthroplasty                                                 |
| TKA     | Total Knee Arthroplasty                                                |
| HA      | Hip Arthroplasty                                                       |
| KA      | Knee Arthroplasty                                                      |
| VTE     | Venous Thromboembolism                                                 |

## 2. Introduction

### 2.1. Background

Over 100,000 total hip and total knee arthroplasty (THA, TKA) procedures are performed each year in Australia. Venous thromboembolism (VTE) comprises deep venous thrombosis (DVT) and pulmonary embolus (PE) and is a recognised serious complication of hip and knee arthroplasty surgery. Patients undergoing THA and TKA receive chemoprophylaxis for VTE prevention, with most patients in Australia receiving either low molecular weight heparin (LMWH) or aspirin (manuscript in preparation).

Guideline recommendations and surgeon preference for VTE prophylaxis vary due to a lack of evidence regarding the comparative safety and effectiveness of these two common chemoprophylaxis agents. Aspirin is a low cost, over-the-counter, safe medication that is easy to take (one oral tablet daily). LMWH requires daily injection (often requiring professional or family support), is more expensive and requires prescription, but has a larger body of evidence of effectiveness. Previous studies comparing LMWH and aspirin have been underpowered for effectiveness and for safety.

Currently, practice guidelines provide conflicting recommendations for VTE prophylaxis. The National Institute of Health and Care Excellence (NICE) guidelines (United Kingdom) now (2018) recommend using LMWH, aspirin or Novel Oral Anticoagulants (NOACs) for VTE prophylaxis in TKA (aspirin is not recommended for THA) whereas aspirin was not recommended in the previous version. In the US, two main guidelines are used: those recommended by the American College of Chest Physicians (ACCP) and those produced by the American Association of Orthopaedic Surgeons (AAOS). Both recommend the use of LMWH, NOACs or aspirin. Previously, the ACCP guidelines recommended against aspirin whereas the AAOS guidelines recommended its use. As of 2012, both guidelines now allow the use of aspirin for VTE prophylaxis, and as a result the prevalence of aspirin prescription has increased. The Australian National Health and Medical Research Council guidelines (2009) did not recommend aspirin, however these guidelines were rescinded in 2016 as they were considered outdated.

A number of systematic reviews (including data from up to 22 trials) have summarised the evidence for VTE prophylaxis in joint arthroplasty, but most do not assess aspirin, despite being commonly used and recommended by some practice guidelines.

Two small systematic reviews were found, including data from six pharmacological trials that had aspirin as a comparator. In both reviews, the evidence was dominated by one trial of 778 patients comparing aspirin to LMWH in THA. This trial was stopped early due to poor recruitment. Furthermore, all patients in the trial received LMWH for the first 10 days before random allocation to aspirin or continued LMWH. This does not reflect the way that aspirin is commonly used in Australia as aspirin is commenced during the acute care period. Another five trials were also described, including a total of 936 patients, but these trials were small, measured different outcomes, and were subject to bias. Both reviews concluded that there is insufficient evidence to support recommendations on the use of

aspirin, and suggest larger trials are needed. A recent large trial compared aspirin to rivaroxaban (a NOAC) for VTE prophylaxis in THA and TKA. A total of 3424 patients were recruited in this cluster-randomised trial, however both groups were treated with rivaroxaban for the first 5 days before being randomised to aspirin or rivaroxaban for the following 2-4 weeks.

While studies using administrative datasets should be interpreted with caution due to risk of coding errors, incomplete data and difficulty fully adjusting for possible confounding, two studies of aspirin using large administrative datasets have been reported. The first, from the US, used data from 93,804 patients undergoing elective total knee replacement surgery. The study compared early (30 day) mortality and VTE between patients given warfarin, LMWH and aspirin, adjusted for patient factors (age, sex, race, VTE risk, comorbidities), institution factors (size, urban/rural) and a separate propensity score. No difference was found in the mortality rates or rates of post-operative bleeding complications between the three groups, and there was no difference in the rate of VTE comparing LMWH to aspirin. A study using data from the National Joint Registry for England, Wales, Northern Ireland and the Isle of Man analysed data from 108,584 patients undergoing THA comparing LMWH to aspirin for VTE prophylaxis using multivariable modelling and propensity score matching. The adjusted analysis showed no significant difference in mortality up to 90 days post-operatively but this difference became significant (favouring LMWH) on propensity score matching. There was no difference in VTE complications or re-operations (up to 90 days) between groups. The reported rates of VTE were very low, possibly due to under-detection.

The existing uncertainty regarding the relative safety and effectiveness of these different medications to prevent VTE following arthroplasty and inconsistencies in available clinical practice guidelines likely contribute to widespread clinical practice variation in Australia. A national survey and recent large cohort study involving 1,900 patients from 19 institutions across Australia (manuscript under preparation) show that nearly all surgeons use some form of chemoprophylaxis, with approximately 80% using LMWH and nearly half using aspirin (approximately 40% of patients had more than one drug). The survey indicated that those using LMWH were more likely to do so for fear of litigation. Aspirin does not require a prescription, is easier for patients to take (tablet rather than injection), is safe and is inexpensive. Therefore, establishing non-inferiority would provide patients with a preferred, effective, safe, cheaper and simpler method of VTE prophylaxis compared to LMWH.

The Australian Orthopaedic Association National Joint Replacement Registry (AOANJRR) was established in 1999 and reports on revision surgery and mortality after joint arthroplasty in Australia, with close to complete national coverage. The AOANJRR has established a system to directly capture data entered by patients pre- and post-operatively; this system is a platform for the conduct of clinical trials and is incorporated as part of the AOANJRR (not a standalone project). The proposed CRISTAL trial will be embedded within the Clinical Trials Platform of the AOANJRR.

## **2.2. Choice of comparators**

Wide practice variation is evident for VTE chemoprophylaxis in Australia due to both surgeon uncertainty in the evidence for effect, and differences in surgeon preference. Aspirin and LMWH are the two most frequently used drugs for VTE prophylaxis in THA and

TKA in Australia. Alternatives, such as warfarin and unfractionated heparin are not commonly used in Australia and are not reflected in practice guidelines in this country. NOACs are an alternative to LMWH and aspirin but are not commonly used in Australia. Given aspirin's popularity, ease of use, safety profile and low cost but lack of evidence of comparative effectiveness against the most commonly recommended drug (LMWH), we considered aspirin to be the most suitable comparator to LMWH for this trial.

### **2.3. Study hypothesis**

Aspirin is non-inferior to LMWH for prevention of VTE after THA and TKA surgery.

### **2.4. Primary aim**

To compare the effectiveness and safety of aspirin to LMWH in preventing symptomatic VTE after primary elective THA and TKA for osteoarthritis (OA).

### **2.5. Secondary aims**

- To compare the effectiveness and safety of aspirin to LMWH in preventing symptomatic VTE after all hip arthroplasty (HA) and knee arthroplasty (KA) including primary, revision and partial arthroplasty, performed for any indication including fracture surgery
- To compare the effectiveness and safety of aspirin to LMWH in preventing symptomatic VTE after revision HA and KA
- Compare the safety (proportion of non-VTE complications) between groups
- An extension of the primary analysis for: HA and KA separately; unilateral and bilateral separately; below-knee DVT, above-knee DVT and PE separately
- To compare the cost effectiveness of aspirin to LMWH for VTE prophylaxis after primary elective THA and TKA for osteoarthritis if aspirin is found to be inferior to LMWH

### **2.6. Trial design**

A pragmatic multicentre, cluster-randomised, crossover, non-inferiority study with a primary endpoint of patient-reported symptomatic VTE at 90 days.

### **3. Methods**

#### **3.1. Setting**

Eligible hospitals (public and private) performing HA and KA in Australia. The study will be nested within the AOANJRR Clinical Trials Platform, an electronic platform for recruitment and data collection for patients undergoing joint replacement surgery.

#### **3.2. Eligibility**

##### Hospital level

- Departmental (or surgeon group) agreement to participate in the study and adhere to study protocols
- Use of intermittent calf compression device intra-operatively and post-operatively until mobile
- Offer mobilisation day 1 post-operatively or earlier
- No change in other practices or protocols relevant to VTE over the course of the study (e.g. tourniquet use, anaesthetic type).

##### Patient level

- Adults (age 18 and older)
- Receiving primary or revision HA or KA for any indication (including for fracture)

##### Exclusion criteria

As a pragmatic study, all patients undergoing revision and primary arthroplasty for any indication during the study period will be included. The only exclusion for a department is if the volume of primary elective THA and TKA for osteoarthritis is less than 250 per year (as this may render the site unable to recruit the required sample size required for the primary analysis within a reasonable timeframe).

At an individual level, patients unsuitable to receive routine prophylaxis will be treated according to local advice and recommendations, as per normal practice. Routine prophylaxis for the purpose of the CRISTAL study includes the LMWH and the aspirin protocols used in CRISTAL. Reasons for not receiving routine prophylaxis include the long-term use of warfarin, NOAC or dual antiplatelet therapy pre-operatively, allergy to the study drug and an underlying medical condition that precludes the use of either drug or the treating doctors consider the patient to be high risk for routine prophylaxis.

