### **3.15. Statistical analysis**

The analysis for the primary objective will be limited to patients undergoing elective primary THA or TKA for a diagnosis of OA, excluding patients for whom the study drugs were contraindicated (e.g., allergy or need for alternative anticoagulant – warfarin, NOAC, dual antiplatelet, for a pre-existing condition). This analysis will test between-group difference in the proportion of cases developing VTE within 90 days for non-inferiority of aspirin at a margin of 1%, on an intention to treat basis.

The primary analysis will use cluster summary methods. These methods estimate the treatment effect using cluster level differences and have been shown to be appropriate for cluster randomised crossover trials with rare outcomes and the intracluster and interperiod correlation coefficients expected in this trial.

Multiple imputation to account for missing outcome data will be investigated, using auxiliary variables gathered from routine AOANJRR data (including age, sex, baseline health, pain and function, diagnosis and surgical factors). Since VTE is rare, if prediction in the imputation models using these auxiliary variables is a problem, no imputation will be performed due to the possibility of bias. Since the most likely reason for loss to follow-up is difficulty in contacting patients postoperatively (rather than any association with treatment assignment or outcome), missing outcome data is expected to be missing completely at random, which will not cause bias in the estimates.

Secondary analyses will be performed for the primary outcome, to test for differences in treatment effect between subgroups of patients: THA only, TKA only and bilateral joint replacement. The analysis method will be the same as the primary outcome and will include an interaction term between subgroup and treatment group.

Further secondary analyses will include an extension of the primary analysis for patients undergoing all forms of HA and KA (total, revision, partial) for any indication (non-elective surgery, non-OA diagnoses) and will include patients for whom the study drug was

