## **STATISTICAL ANALYSIS PLAN**

### **Patient Populations and Subgroups for Analyses**

The total patient population for CRISTAL comprises all patients undergoing HA or KA at participating institutions over the duration of the study, regardless of whether these patients were registered or eligible to receive the study drug (defined as population 5, see Figure 1).

Within this total population, the following populations will be used to form the basis of the analyses:

- Registered patients undergoing any form of HA or KA (including partial or revision surgery, for any indication) regardless of eligibility to receive the study drug (population 4)
- Registered patients undergoing any form of HA or KA (including partial or revision surgery, for any indication) who were eligible to receive the study drug (population 3)
- Registered patients undergoing elective primary THA or TKA (for any indication) who were eligible to receive the study drug (population 2)
- All registered patients undergoing elective primary THA or TKA for a recorded diagnosis of osteoarthritis (OA) who were eligible to receive the study drug (population 1)

These populations are represented diagrammatically in Figure 1.

**Figure 1.** Patient populations within CRISTAL

[figure not shown]

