### **Analysis principles**

Data will be analysed according to the intention-to-treat principle with clusters analysed according to assigned group allocation. Although hospital and patient protocol deviations will be recorded, no as-treated analyses will be performed, as there are no verified data available to determine whether individual patients received the assigned study drug for the full period, given the pragmatic nature of the trial. The timing of analyses will be stratified by follow-up time of the outcomes measured (90 days and 6 months). The difference in absolute risk for symptomatic VTE between each group and 95% confidence intervals (upper and lower) will be examined to determine if the non-inferiority margin is met.

Continuous variables will be summarised using standard measures of central tendency and dispersion, using either mean and standard deviation or median and interquartile range. Categorical variables will be summarised by frequencies and percentages.

Analyses will be performed using SAS version 9.4 (SAS Institute, Cary USA) and R (R Foundation for Statistical Computing Platform) version 4.0.2 or higher.

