### **Trial profile and baseline characteristics**

The flow of participating hospitals (including losses and exclusions) through the study and participating patients will be reported in line with the Consolidated Standards of Reporting Trials (CONSORT) statement (Figures 2 and 3).

Baseline characteristics of participating clusters, including number of annual HA and KA procedures performed in the year prior to trial commencement, hospital type (public or private hospital), initial treatment allocation and whether the hospital achieved crossover are shown in Table 1. This table also shows the number of patients registered for population 1 (the population used for the sample size calculation) by each participating hospital and the overall registration rate of each hospital will be presented as outlined. The overall registration rate describes the number of registered patients undergoing any HA or KA procedure (population 4) divided by the number of patients who underwent any HA or KA procedure over the duration of the trial at participating hospitals (regardless of whether they were registered – population 5). Hospital names will remain anonymous.

Descriptive statistics of baseline patient characteristics for all registered patients eligible to receive the study drug (population 3) will be presented by prophylaxis group (Table 2).

**Figure 2.** Flowsheet of participating hospitals

[figure not shown]

**Figure 3.** Flowsheet of patients within population 1†

[figure not shown]

† Population 1 refers to registered patients undergoing primary THA or TKA for a diagnosis of OA, who are eligible to receive the study drug

**Table 1.** Number of registered patients for population 1† by treatment group and overall registration rate for each participating hospital

| Hospital     | Number of HA and KA Procedures performed (2018) | Insurance Status | Initial Treatment Allocation | Crossover Achieved | LMWH Group (Population 1) | Aspirin Group (Population 1) | Overall Registration Rate (combined for both groups) |
|--------------|-------------------------------------------------|------------------|------------------------------|--------------------|---------------------------|------------------------------|------------------------------------------------------|

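### Entry to population 1 depends partly on a clinical eligibility judgement made with the arm known, and the plan leaves open where patients judged high risk belong

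*Supplement*

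**What the plan says.** **Receipt of the drug (final protocol 3.2, Exclusion criteria).** The rule for individual patients is that "patients unsuitable to receive routine prophylaxis will be treated according to local advice and recommendations, as per normal practice". The listed reasons are long-term warfarin, NOAC or dual antiplatelet use, allergy to the study drug, a condition precluding either drug, or that "the treating doctors consider the patient to be high risk for routine prophylaxis". No criteria are given for the last. The section does not say that these patients leave the primary analysis.

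**Primary analysis set (final protocol 3.15).** The analysis covers elective primary THA or TKA for OA, "excluding patients for whom the study drugs were contraindicated (e.g., allergy or need for alternative anticoagulant" being the exclusion. The list of examples is open, and the analysis is described as intention-to-treat.

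**Final SAP.** Under Patient Populations, population 1 is registered patients having elective primary THA or TKA "for a recorded diagnosis of osteoarthritis (OA) who were eligible to receive the study drug (population 1". Under Participating Hospitals and Patient Registration, the ineligible are those on a long-term NOAC, warfarin or dual antiplatelet therapy, and those with a medical contraindication to either drug, with allergy and thrombophilia as examples. The Figure 1 legend names the same two groups. Neither place mentions patients judged to be at high risk. Under Analysis principles, "Data will be analysed according to the intention-to-treat principle", with clusters analysed by assigned allocation.

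**Knowledge of the arm.** Final protocol 3.12 says that sites are not blinded. The SAP (Randomisation and allocation) says that each site learned its first arm the week before it began registering patients.

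**The concern.** The exclusion acts on individual patients after the hospital's arm is known. Anticoagulant history is a recorded fact, but whether a comorbidity precludes a drug is a judgement, and here the drug in question is known. A doctor might exempt patients with high VTE risk more readily in aspirin periods, or patients with high bleeding risk more readily in LMWH periods. Analysing clusters as allocated does not protect against patients being removed within a cluster-period.

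The wording does not settle the matter. The SAP refers both to eligibility for the allocated drug and to contraindication to either drug. Protocol 3.3 has the site notify the Registry when a contraindication requires the study drug to be withheld. Taken literally, a patient allergic to aspirin triggers that notice in an aspirin period but not in an LMWH period. The either-drug rule would be symmetric if both drugs were screened in both periods, but no procedure for this is described.

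At stake is the primary non-inferiority conclusion: selective loss of high-VTE-risk patients from the aspirin arm would lower its observed rate.

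**Working it through.** **1. Where each class of patient goes.**

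| Class | Protocol 3.2 | Protocol 3.15 | SAP population 1 |
|---|---|---|---|
| Long-term warfarin, NOAC, dual antiplatelet | Local treatment | Excluded | Excluded |
| Allergy, other contraindication | Local treatment | Excluded (open list) | Excluded |
| Judged high risk by treating doctors | Local treatment | Not named | Not named |

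The second row rests partly on judgement. The third row is undecided: two analysts could build different primary sets.

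**2. The plan's own figures.** Inputs from the SAP (Power and sample size): 2.5% v 1.5%, one-sided 0.025, power 90%, ICC 0.01, interperiod correlation 0.008, 31 clusters.

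- Individual randomisation, pooled variance under the null: n = [1.960 × √(2 × 0.02 × 0.98) + 1.2816 × √(0.025 × 0.975 + 0.015 × 0.985)]² / 0.01² = 4,117 per group, as stated.
- Cluster crossover: 31m = n[1 + 0.01(m − 1) − 0.008m], so m = 0.99 × 4,117 / (31 − 0.002 × 4,117) = 179.03, rounded up to 180. Then 180 × 31 × 2 = 11,160, as stated.

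The sample size is not in question. It supplies the standard error used below.

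**3. Size of a possible shift.** The documents give neither an exemption rate nor the risk in exempted patients, so both are assumed. Let d be the extra share removed from the aspirin arm only, r the VTE rate in those removed, and p = 2.5%. Then shift = p − (p − dr)/(1 − d) = d(r − p)/(1 − d). In percentage points towards non-inferiority:

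| d | r = 3% | r = 5% | r = 7.5% | r = 10% |
|---|---|---|---|---|
| 1% | 0.005 | 0.025 | 0.051 | 0.076 |
| 2% | 0.010 | 0.051 | 0.102 | 0.153 |
| 3% | 0.015 | 0.077 | 0.155 | 0.232 |
| 5% | 0.026 | 0.132 | 0.263 | 0.395 |

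Excess removal in LMWH periods reverses the sign. At d = 5%, r = 10% and p = 1.5%, the difference moves 0.05 × (0.10 − 0.015)/0.95 = 0.45 points against aspirin.

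**4. Effect on the non-inferiority test.** Design SE = √[(0.025 × 0.975 + 0.015 × 0.985)/4,117] = 0.308 points. If the true difference equals the 1-point margin, P(non-inferiority declared) = Φ(shift/SE − 1.96):

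| Shift (points) | Probability |
|---|---|
| 0 | 2.5% |
| 0.05 | 3.6% |
| 0.10 | 5.1% |
| 0.20 | 9.5% |
| 0.40 | 25% |

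This uses the planned precision. The trial stopped early, so the actual SE will differ.

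**5. What the planned analyses cover.** Populations 2 and 3 keep the eligibility filter. Population 4 removes it but adds partial, revision and non-OA surgery. The four sensitivity analyses concern site volume, registration rate, repeat compliance audits and long-term aspirin use. None analyses VTE in all registered elective primary OA patients regardless of eligibility.

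**The case against.** A reader might infer that population 1 drops every patient judged at high risk. The documents do not say so. The clause in protocol 3.2 governs who receives the drug, and the SAP's account of ineligibility omits it. The SAP also records patients who did not receive the correct drug as protocol deviations and keeps intention-to-treat, so it is equally possible to read such patients as staying in.

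The clause also came late. The amendment log dates it to 29 October 2020; recruitment ran from April 2019 to December 2020, about 20 months. If it applied for two of them and recruitment was even, a trial-wide excess of 5 points from this clause alone would need 5 × 20/2 = 50 points within that window. The contraindication exclusion is therefore the firmer basis for the point.

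A reader might also infer that the plan conceals differential selection. It does not. SAP Table 4 gives numbers by arm for populations 3 and 4, which differ only in drug eligibility, so ineligible counts by arm follow by subtraction. Table 1 gives population 1 by hospital and arm. Table 2 shows previous VTE by arm in population 3, which has the same filter. Figure 3, the population 1 flowsheet, was not visible in the text reviewed and may show more. What is missing is reasons by arm, the counts within the target surgery, and registration by arm: Table 1 has only "Overall Registration Rate (combined for both groups".

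Population 4 is a real support. It uses the same method, and protocol 3.3 expects about 250 of 300 patients per group (83%) to be eligible for the primary analysis. It still answers a wider question than the primary one.

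Finally, a recorded contraindication is itself recorded by unblinded clinicians, so a tighter definition reduces the exposure without removing it. That stands, and it is why the added analysis without the filter matters most.

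**Conclusion.** The point holds as a risk and an ambiguity. Population 1 is restricted after allocation, partly by judgement at sites that know their arm; it is intention-to-treat for clusters but not for every patient within them. The standing of patients judged at high risk is undefined.

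Nothing in the documents shows that exclusions differed by arm, or in which direction. Equal exclusion of similar patients in both arms would cause no such shift. Over the assumed range (1% to 5% excess removal from the aspirin arm, 3% to 10% risk) the shift is about 0.005 to 0.40 points: negligible at one end, material against a 1-point margin at the other. Harsher inputs give more, for example 0.10 × (0.08 − 0.025)/0.90 = 0.61 points, but the documents offer no support for them. To call the primary analysis biased, or simply not intention-to-treat, would go beyond the text.

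**What to change.** Amend the SAP before database lock, which its Blinding section allows:

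1. Define ineligibility for population 1 only by recorded pre-operative facts applied identically in both periods: long-term warfarin, NOAC or dual antiplatelet use, or a recorded contraindication to either drug, whichever is allocated. State that patients exempted on clinical judgement alone stay in population 1 under the hospital's allocated arm.
2. Add a sensitivity analysis of the primary outcome, by the same composite method, in all registered elective primary THA/TKA for OA regardless of drug eligibility.
3. Tabulate ineligible patients with reasons, and registration rates, by arm. The added analysis still depends on who was registered, so the registration rates are needed to read it.

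The cost is SAP wording, one more run of an existing method, and tables from data that the sites and registry already hold. The statistical cost is slight dilution, in the added analysis and from exempted patients retained in population 1. No change to any patient's treatment is proposed.
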